### Phase 3: Intervention Evaluation

We will conduct a pilot hybrid type 1 effectiveness-implementation cluster-randomized controlled trial [20] to assess intervention acceptability and feasibility (clinics: N=4; adolescents: N=120). The cluster-randomized controlled trial design minimizes the risk of contamination among participants in different arms and is ideal when settings are similar in terms of population characteristics. These trials are frequently used when interventions are to be carried out at the level of whole groups. Implementation science hybrid designs assess intervention effectiveness in real-world settings and document barriers and facilitators to delivery and sustainability [20]. Considering that our goal is to disseminate the intervention widely, we must understand the contexts that influence success and failure, so that we can plan for them and mitigate weaknesses accordingly.

We will enroll 120 adolescents across 4 clinics; 2 clinics will be randomized to implement the intervention condition, and 2 clinics will be randomized to a time-attention control. All African American patients unvaccinated for HPV (aged 15-26; all genders) will be approached to enroll in the study when they come in for a visit, regardless of the purpose of that clinical visit. After informed consent is collected from adolescents, we will collect preintervention, immediately postintervention, 2-month postintervention, and 6-month postintervention survey data related to the behavior change objectives -- increased knowledge of vaccines, reduced stigma, and increased motivation, which all result in improved vaccine confidence and higher vaccination rates — in addition to participant demographics and known potential associates of vaccination or vaccine hesitancy. We will collect design metrics to assess feasibility and acceptability, informed by the Bowen framework [27] (Figure 2).

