### Phase 3: Data Management and Quantitative Analysis

A descriptive analysis of all study feasibility and outcome variables will be summarized by using means and SDs for continuous measures and frequencies and percentages for categorical measures. Between-group differences will be compared by using standard 2-tailed cluster analyses. Further, 2-sample tests for proportions [28] will be used to compare initial vaccination acceptance, the indication of dose completion, and study dropout. An adjusted McNemar test [29] will be used to determine if the intervention group had any changes in vaccine knowledge post intervention. Similar analyses will be used in the control group, and the two groups’ changes will be examined. For any continuous measure (eg, stigma), 2-sample *t* tests [30] will be used, and appropriate assumptions will be validated. Factors related to unexpected design or study implementation issues, such as systematic enrollment issues at clinics or differential times between patients’ first visit and their follow-up resulting from issues beyond common follow-up issues, will be assessed. If it is determined that these issues require analysis adjustment, we will use generalized estimating equations to compare group differences in all measures while adjusting for these factors. Generalized estimating equations require all missing data to be missing completely at random; however, as our primary outcome relates to initial vaccination acceptance, we do not expect any missingness. Likewise, we will assume that study dropout is an indicator of incomplete dosing. Missing values for other outcomes will be examined, and if missingness at random can be assumed, multiple imputations [31] will be used.

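### The only test named for vaccine knowledge is a before-after McNemar test within each arm, on two clinics at a time; the between-arm comparison has no named method

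*Protocol article*

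**What the plan says.** All statements come from the protocol article.

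- Phase 3: Data Management and Quantitative Analysis names one test for knowledge: "An adjusted McNemar test [29] will be used to determine if the intervention group had any changes in vaccine knowledge post intervention". It continues: "Similar analyses will be used in the control group, and the two groups’ changes will be examined".
- The same section has a general sentence, not tied to any outcome: "Between-group differences will be compared by using standard 2-tailed cluster analyses". If unexpected design or implementation problems are judged to need adjustment, "we will use generalized estimating equations to compare group differences in all measures while adjusting for these factors".
- Phase 3: Intervention Evaluation sets the design: "We will enroll 120 adolescents across 4 clinics", and "2 clinics will be randomized to implement the intervention condition, and 2 clinics will be randomized to a time-attention control".
- On timing, the same section says "we will collect preintervention, immediately postintervention, 2-month postintervention, and 6-month postintervention survey data". Better vaccine knowledge is among the behavior change objectives listed there.
- The analysis section gives initial vaccination acceptance as the primary outcome, so knowledge is not primary.

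**The concern.** The hypothesis attached to the named test is that the intervention arm changed from its own baseline. The trial has a time-attention control so that contact, repeated surveying and the passage of time can be separated from the intervention. A test inside one arm makes no use of that. Knowledge is surveyed before the session, straight after it and twice more, so some gain from seeing the same questions again is plausible in both arms.

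Two things are at stake. First, a gain that both arms share could be read as an intervention effect, or a significant result in one arm and a non-significant one in the other could be read as a difference between arms. Second, each within-arm test has two clusters, too few to estimate how much change varies between clinics. Knowledge is the information step of the theory behind the intervention, and the feasibility table lists effect sizes and effects on key intermediate variables among the pilot's sample outcomes. A within-arm p-value gives no between-arm effect size.

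**Working it through.** The article gives no alpha, power, effect size or between-clinic variance for knowledge, so there is no figure of the plan's own to reproduce.

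**Inputs from the document.** 120 participants, 4 clinics, 2 clinics per arm, two-tailed testing.

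**Assumptions.** Alpha 0.05. Equal clinics: 120/4 = 30 per clinic, 120/2 = 60 per arm. Knowledge treated as a binary item, as McNemar requires.

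**1. Two within-arm verdicts under the same true gain.** If each test has power P and the arms are independent, P(exactly one significant) = 2P(1-P).
- P = 0.5: 2 × 0.5 × 0.5 = 0.50. The pattern of intervention significant, control not, has probability 0.25.
- P = 0.8: 2 × 0.8 × 0.2 = 0.32, and 0.16 for that pattern.

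Simulation with unadjusted McNemar tests (20,000 runs; wrong-to-right and right-to-wrong proportions of 0.25/0.12 and 0.30/0.10, the same in both arms): exactly one arm significant in 40% to 49% of trials; intervention only in 20% to 25%.

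**2. What two clinics do to each within-arm test.** Let d1 and d2 be the net changes in the two clinics. The exact form in reference 29 is not shown, so three forms were tried.

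(a) Variance from the sum of squared cluster differences: statistic = (d1 + d2)² / (d1² + d2²). Since (d1 + d2)² ≤ 2(d1² + d2²), it cannot exceed 2. P(chi-square, 1 df > 2) = 0.157, so p is never below 0.157 however large the change.

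(b) Empirical variance about the mean of the two clinics, referred to chi-square with 1 df: the statistic is a squared t with 1 df. True type I error = P(|t, 1 df| > 1.96) = 1 - (2/π) × arctan(1.96) = 0.300; simulated 0.31.

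(c) No adjustment for clinic. With 0.15/0.15 (no true change) the sampling variance of the arm's mean change is 0.30/60 = 0.005. A between-clinic SD s in net change adds s²/2.
- s = 0: type I error 5%.
- s = 0.10: added variance 0.005, inflation 2, P(|Z| > 1.96/√2) = 0.166; simulated 16%.
- s = 0.20: added variance 0.02, inflation 5, P(|Z| > 1.96/√5) = 0.38; simulated 36% to 37%.

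The simulation moved the gain proportion with SD 0.05 or 0.10 and the loss proportion equally in the opposite direction. The SD of net change is therefore about twice those values, as shown here. Truncating proportions near zero explains the slight shortfall from 0.38.

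**3. The between-arm alternative.** A t test on four clinic summaries has 4 - 2 = 2 df and critical value 4.30. When both arms changed equally, its simulated type I error was 4.7% to 5.2% in all nine scenarios (three gain/loss pairs, three levels of clinic variation).

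Its precision is poor. With 0.25/0.12 and no clinic variation, the variance of individual change is 0.37 - 0.13² = 0.353. The standard error of the difference is √(2 × 0.353/60) = 0.108, and the 95% half-width is about 4.30 × 0.108 = 0.47 on the scale of net change in proportion correct. Clinic variation widens it; baseline adjustment may narrow it.

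**The case against.** The strongest reply is that the plan does not overlook the randomised comparison. The sentence after the McNemar test says the two groups' changes will be looked at together, a general sentence promises between-group cluster analyses, and generalized estimating equations are a conditional fallback for all measures. A condensed article may leave the detail to an analysis plan. This stands in part: a reader might infer that the plan ignores the arm comparison, and the text does not support that. It does not remove the point, because what the article fixes for knowledge is a test of a different hypothesis. For vaccination acceptance and for continuous measures the same section does name two-sample tests.

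A reader might also infer that clustering was forgotten. The word adjusted suggests otherwise; the difficulty is too few clusters.

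A third tempting reading is that a knowledge score will be dichotomised, with loss of information. The article never says how knowledge is recorded. It gives knowledge a binary test and treats continuous measures separately, which fits items scored right or wrong. No such loss can be claimed.

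The harms in the working also exclude one another. If form (a) is used, power at 0.05 is zero and discordant verdicts cannot arise. The 2P(1-P) figures apply only to a form that can reject.

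Finally, this is a pilot, no stated decision turns on a knowledge p-value, and the alternative also has only four clinics. All true, and reflected in the severity.

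**Conclusion.** The point holds in this form: the named inference on knowledge is within-arm on two clinics, and the between-arm comparison is mentioned without a method. The named test cannot isolate an intervention effect, and its p-value is unreliable in each form tried: it cannot reach 0.05 in one, has about 30% type I error in another, and runs from 5% to about 36-37% in the third as clinic variation grows. Which applies is unknown because the cited form is not shown, so even the direction of the error is uncertain. Where the tests can reject, reading the two verdicts against each other misleads in up to 50% of trials with equal true gains.

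The figures rest on assumed alpha 0.05, equal clinics, and assumed change proportions and between-clinic SDs. The two-clinic count and the within-arm hypothesis come straight from the article. Severity is low to moderate: knowledge is an intermediate outcome, but a stated objective of the intervention.

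**What to change.** Make the knowledge analysis the difference between arms at each post-intervention time (immediate, 2 months, 6 months), adjusted for the preintervention value, on whatever scale knowledge is recorded and undichotomised if it is a score. Use clinic as the unit at the second stage: adjust for the preintervention value at participant level, summarise by clinic, and compare the four summaries with 2 df. Report an estimate with a 95% confidence interval. Show within-arm changes descriptively, without p-values.

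The cost is a change of analysis wording; the surveys are already planned in both arms. The drawback is a wide interval and little power with four clinics, and near-normality of clinic summaries cannot be checked with so few. That is a limit of the design, and estimation suits the pilot's aim better than two within-arm tests do.

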**Figure 2 figure2:**
[figure not shown]
Randomized controlled trial study flow (phase 3).

All participant data collection will occur electronically. Informed consent will be collected via Adobe Sign (Adobe Inc), and self-report data will be collected through a standardized Qualtrics (Qualtrics International Inc) survey. Pre- and postintervention data collection, which will occur in clinics, will be conducted with iPads (Apple Inc) that are dedicated to the study site. Data will be immediately uploaded to a secure database through wireless connectivity. Self-report data to be collected at 2 and 6 months post intervention will be captured by using the same standardized Qualtrics survey that will be used in clinics; the direct survey link will be shared via text or email, depending on the participants’ preferences.

We will conduct exit interviews with clinic health providers to assess barriers and facilitators to implementation specifically to inform regional dissemination.

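### The survey measures are collected once before and three times after the intervention, but the default tests use one post-intervention wave at a time, name no wave, and keep the repeated-measures model as a contingency

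*Protocol article*

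**What the plan says.** Under Phase 3: Intervention Evaluation, the protocol article states: "we will collect preintervention, immediately postintervention, 2-month postintervention, and 6-month postintervention survey data related to the behavior change objectives". The text below Figure 2 in that section confirms that the later waves repeat the in-clinic instrument: "Self-report data to be collected at 2 and 6 months post intervention will be captured by using the same standardized Qualtrics survey". The scales are therefore repeated measures, with one baseline and three follow-ups.

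Under Phase 3: Data Management and Quantitative Analysis, the default methods are:

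- **Continuous measures:** the rule begins "For any continuous measure (eg, stigma" and names 2-sample t tests. It mentions neither a wave nor a change score.
- **Vaccine knowledge:** an adjusted McNemar test is used "to determine if the intervention group had any changes in vaccine knowledge post intervention". The same is done in the control group and the two groups' changes are then examined. Which follow-up wave is meant is not said.
- **GEE:** "If it is determined that these issues require analysis adjustment, we will use generalized estimating equations to compare group differences in all measures". The triggers given are enrollment problems at clinics and unusual follow-up timing.
- **Missing data outside the primary outcome:** "Missing values for other outcomes will be examined, and if missingness at random can be assumed, multiple imputations" will be used.

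The primary outcome is initial vaccination acceptance. According to the Medical Records section, vaccination is read from clinic records over the 6-month period.

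**The concern.** The design pays for four survey waves, but the default analysis is chosen as if there were one or two. A 2-sample t test compares the arms at a single occasion. A McNemar test compares one pair of occasions within an arm. Neither brings the three follow-ups together, and the t test as written leaves the baseline out. With only two clinics per arm, a baseline difference between arms is quite possible, so omitting the baseline matters for bias as well as precision.

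Because no wave is designated, the analyst can choose after seeing the data. The immediate wave is completed in the clinic straight after the content, so it may show recall that has gone by month 2 or 6. Nothing in the article stops that wave from standing as the effect on knowledge or stigma. What is at stake is the pilot's estimate for the intermediate variables, which the Bowen table lists as a purpose of the limited efficacy testing.

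**Working it through.** The article gives no alpha, effect size, SD, dropout rate or sample-size derivation for these measures, so there is no stated figure to reproduce.

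**Inputs from the article:** three post-intervention waves; 120 participants in 4 clinics, 2 clinics per arm; 2-tailed testing.

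**Assumptions:** alpha 0.05; 120/2 = 60 per arm; equal correlation r between waves; clustering ignored.

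**1. False-positive chance for one measure if all three waves are tested.** If the waves are independent, it is 1 − (1 − 0.05)^3 = 1 − 0.857 = 0.143. For correlated waves, three equicorrelated two-sided z tests were simulated (2,000,000 draws):

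| r between waves | P(at least one p < 0.05) |
|---|---|
| 0 | 14.3% (exact) |
| 0.3 | 13.6% |
| 0.5 | 12.5% |
| 0.7 | 10.9% |
| 0.9 | 8.4% |

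One pre-named contrast returns this to 5%. Keeping three separate tests would need 0.05/3 = 0.0167 for each.

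**2. Upward bias from picking the best wave.** Suppose the true effect is the same at all three waves. The largest of three equicorrelated estimates then exceeds it on average by 0.846 × √(1 − r) standard errors. In SD units the standard error of an arm difference is √(2/60) = 0.183.

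- r = 0.5: 0.846 × 0.707 × 0.183 = 0.11 SD
- r = 0.7: 0.846 × 0.548 × 0.183 = 0.08 SD

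**3. What the earlier waves are worth when month 6 is missing.** Suppose a fraction d is missing at 6 months and both earlier follow-ups are complete. The share of 6-month variance that they predict is R² = 2r²/(1 + r), which is 0.333 at r = 0.5 and 0.576 at r = 0.7. The variance of the arm mean using them is (1 − R²)/[60(1 − d)] + R²/60, and its reciprocal is the effective n.

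| d | n per arm, 6-month responders only | effective n, r = 0.5 | effective n, r = 0.7 |
|---|---|---|---|
| 20% | 48 | 51.4 | 54.3 |
| 30% | 42 | 46.7 | 50.8 |

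For example, at d = 20% and r = 0.5: 0.667/48 + 0.333/60 = 0.0194, and 1/0.0194 = 51.4. The gain is moderate. It is lost only if neither the planned imputation nor GEE uses those waves.

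**4. What the baseline is worth.** If baseline and follow-up correlate at r, adjustment leaves a fraction 1 − r² of the within-clinic variance: 1 − 0.25 = 0.75 at r = 0.5, and 1 − 0.49 = 0.51 at r = 0.7.

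**The case against.** The best counter-argument is that this is a condensed article and that the time point for secondary scales is often settled in the analysis plan, which is not shown. That stands for the missing wave taken alone. It does not dispose of the point, because the article does choose methods: tests for one or two occasions as the default, and the model that could handle all waves only if something goes wrong. If the trial runs smoothly, the less suitable tests remain the plan.

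Several stronger readings are tempting, and the documents do not support them.

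- A reader might infer that every measure will be tested at all three waves. The article never says so; a t test fits equally with one chosen wave or a change score. For knowledge, the text below Figure 2 uses pre- and postintervention for the in-clinic pair, so a single pair is a plausible reading. The error rates above are therefore conditional.
- A reader might infer that participants who answer at 2 months but not at 6 add nothing to the 6-month comparison. The planned multiple imputation could use their earlier answers. The article does not say that it will, so the loss is possible but not established.
- A reader might count four measures at three waves as 12 tests and quote 1 − 0.95^12 = 46%. That requires independence, and it adds multiplicity across measures, which is a separate matter. One contrast per measure would still leave four tests.

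It is also fair to say that month 6 is not the only defensible time point. Under the trial's theory, information and motivation precede vaccination, and some vaccinations may occur before the 6-month survey.

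**Conclusion.** The concern holds in a limited form. The default tests for the survey measures are weaker than the data the trial will collect, no wave carries the result, and the model that would use all waves is held back for implementation problems. If all three waves were tested at an assumed 0.05, the per-measure false-positive chance would be about 8% to 14%. Picking the best wave would inflate the effect size by about 0.08 to 0.11 SD, assuming 60 per arm, between-wave correlation of 0.5 to 0.7 and no clustering. A reader might take this as a threat to the trial's main result. It is not one: vaccination acceptance comes from medical records and is not tested wave by wave, and this is a pilot of acceptability and feasibility. The consequence is confined to the secondary survey measures and to the effect sizes carried forward from them.

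**What to change.** In Phase 3: Data Management and Quantitative Analysis:

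1. For each survey measure, replace the default t or McNemar test with one repeated-measures analysis that has arm, wave and arm by wave, is adjusted for the preintervention value, and uses a link suited to the scale (a binary model if knowledge is scored right or wrong).
2. Make inference respect the four clinics, for example through clinic-level summaries. These leave 4 − 2 = 2 degrees of freedom, so the emphasis should be on estimates and intervals.
3. Name one contrast per measure in advance. Six months is a reasonable choice because it matches the vaccination window; the investigators may justify another wave.
4. Report the remaining waves as a descriptive trajectory.
5. State that the multiple imputation model includes the baseline and all earlier waves. This matters particularly if GEE is used, since the article itself says that GEE needs data missing completely at random.

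The cost is a few sentences of analysis wording, with no new data and no change to conduct. The small downside is that an effect seen only at a wave other than the named one cannot be the headline result.

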### Phase 2: Intervention Development

We will use intervention mapping [24] and the designing for dissemination [25] approach, which will be informed by data from the first phase, to develop the intervention. We chose the 4-step intervention mapping model to inform the development process [24]. Intervention mapping is a systematic, iterative process characterized by contextual evaluation, stakeholder feedback, and the use of theories and evidence, making it an excellent fit for implementation science trials in real-world settings [24]. Using intervention mapping will allow us to prioritize key targets while considering barriers to testing and prevention.

The tablet-based intervention will include 3 modules consisting of multiple subtopics, deliver tailored (ie, for youth and rural contexts) digital content in the clinic waiting room, include motivational interviewing [26] components that are effective in evoking behavior change while being acceptable to adolescents and parents, and include ongoing support through text reminders. The intervention will be designed to reduce health provider burden and to consider practice and environmental limitations. We anticipate drafting 2 to 3 versions of the intervention before finalizing a version for pilot-testing. Each version will be reviewed by a group of adolescents and clinical health providers (estimated number of reviewers per version: range 4-6).

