### Medical Records

We propose to collect data on vaccination from medical records at partner clinics. We will request records from partner clinics, and a member of each clinic will extract them for evaluation. The research team will review medical records for evidence that participants accepted vaccination during the 6-month study period, as well as evidence of whether the participants completed the vaccine series.

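### If triggered, the fallback GEE may adjust the arm comparisons, vaccination included, for time to follow-up, which arises after randomisation and which the intervention could affect

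*Protocol article*

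**What the plan says.** All of this is in the protocol article.

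- **Main tests** (Phase 3: Data Management and Quantitative Analysis). Initial vaccination acceptance, dose completion and dropout are compared with two-sample tests for proportions, and continuous measures with two-sample t tests. None of these adjusts for timing.
- **Fallback** (same section). The factors are introduced as "Factors related to unexpected design or study implementation issues, such as systematic enrollment issues at clinics", and the second example is "differential times between patients’ first visit and their follow-up resulting from issues beyond common follow-up issues, will be assessed". The switch is conditional: "If it is determined that these issues require analysis adjustment". If it is made, "we will use generalized estimating equations to compare group differences in all measures while adjusting for these factors". The section names initial vaccination acceptance as the primary outcome, so it is among the measures covered.
- **Randomisation** (Phase 3: Intervention Evaluation). "2 clinics will be randomized to implement the intervention condition, and 2 clinics will be randomized to a time-attention control".
- **Intervention** (Phase 2: Intervention Development). It has motivational interviewing components and will "include ongoing support through text reminders".
- **Vaccination outcome** (Medical Records). The team looks for "evidence that participants accepted vaccination during the 6-month study period".

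**The concern.** The trial asks whether the intervention raises vaccination and changes the intermediate measures. An arm comparison at equal follow-up time answers that question only if the arm leaves follow-up time alone. Clinics are randomised before any youth has a follow-up time, and one arm receives reminders and motivational content, so the condition cannot be taken for granted. Nothing in the section limits the adjustment factors to those known before the intervention, and nothing keeps the unadjusted comparison as the main result once the fallback is invoked.

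Two kinds of harm are possible. If earlier follow-up itself leads to vaccination, adjustment removes that part of the effect. If an unmeasured trait such as motivation drives both early follow-up and vaccination, adjustment sets reminder-prompted youths against more motivated controls and pushes the estimate against the intervention. The pilot looks for a signal of effectiveness and plans to estimate an effect size, so either error could mislead a decision on scale-up.

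**Working it through.** The article gives no effect size, power or alpha for the 120 youths, so there is no figure of its own to reproduce. The check has a reading part and an illustration.

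**Reading**

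1. Time to follow-up is observed after randomisation, because clinics are allocated before youths are followed.
2. It is named as a possible adjustment factor, and the fallback applies to all measures.
3. The limit to causes beyond the usual follow-up problems governs when adjustment is considered. The article gives no way to split a youth's interval into an external part and a part due to the arm. If the observed interval is the covariate, it carries both.
4. Vaccination is read from records over a 6-month period. Time to follow-up therefore does not set the observation time for that outcome.

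**Illustration: timing affects vaccination.** All effect inputs are assumed. T is time to follow-up in SD units, and the intervention shortens it by s. The model is logit P(vaccinated) = -1.4 + d × arm + b × T, with 400,000 simulated youths per scenario and no clustering.

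| d | s | b | Control | Intervention | OR without T | OR with T |
|---|---|---|---|---|---|---|
| 0 | 0 | -1.0 | 0.236 | 0.236 | 1.00 | 1.00 |
| 0 | 0.25 | -0.5 | 0.209 | 0.230 | 1.13 | 1.00 |
| 0 | 0.5 | 0 | 0.198 | 0.198 | 1.00 | 1.00 |
| 0 | 0.5 | -1.0 | 0.238 | 0.321 | 1.52 | 0.99 |
| 0 | 1.0 | -1.0 | 0.236 | 0.416 | 2.31 | 1.00 |
| 0.5 | 0 | -1.0 | 0.237 | 0.321 | 1.53 | 1.65 |
| 0.5 | 0.25 | -0.5 | 0.210 | 0.325 | 1.81 | 1.64 |
| 0.5 | 1.0 | -1.0 | 0.236 | 0.520 | 3.51 | 1.64 |

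Hand check of the fifth row: (0.416/0.584) / (0.236/0.764) = 0.712/0.309 = 2.31.

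The part of the effect carried by timing disappears on adjustment. With s = 0 and no direct effect, both odds ratios are 1.00. With s = 0 and d = 0.5, the gap between 1.53 and 1.65 is logistic non-collapsibility, not bias.

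**Illustration: shared cause.** T does not affect vaccination and the arm has no effect on it, but an unmeasured factor drives both T and vaccination with strength g.

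| s | g | OR without T | OR with T |
|---|---|---|---|
| 0 | 1.0 | 1.00 | 1.00 |
| 0.5 | 0.5 | 1.01 | 0.91 |
| 0.5 | 1.0 | 1.00 | 0.80 |
| 1.0 | 1.0 | 1.00 | 0.63 |

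**At trial size.** This uses 60 per arm (120/2, an equal split assumed), two-sided 5% and no clustering, with ranges over runs of 2,000 and 3,000 replicates.

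- Direct log odds ratio 0.6 and 0.8 log-odds per SD of earlier follow-up: a 0.5 SD shift takes power from 58% to 25-28%, and a 0.8 SD shift from 79-80% to 26-29%.
- Effect wholly through timing (1.0 SD shift, 1.5 log-odds per SD): 80-81% to 5-6%. Adjusted power near 5% follows by construction.
- No true effect, motivation correlated 0.5 with timing, shift 0.5-1.0 SD: rejection is 7-24% adjusted against about 5% unadjusted, with adjusted log odds ratios of -0.21 to -0.61. At correlation 0.3 it is 5-11%.
- No shift in timing: about 5% either way.

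**The case against.** The strongest reply is that this is a contingency, not the plan. The planned tests are unadjusted. Time is one of two examples, limited to unusual causes, and if the only problem is enrolment at a clinic it need not enter. All of that stands. A reader might infer that the GEE always adjusts every comparison for time to follow-up, or that it necessarily tests a different hypothesis; the text supports neither. The null changes only if the arm shifts timing and timing is related to vaccination.

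The article also does not say that the reminders aim at visit or survey timing, or whether control youths receive messages. The only scheduled follow-ups it describes are surveys at 2 and 6 months, sent by link. Answering a survey sooner is not an obvious route to vaccination, and a youth vaccinated at the enrolling visit has the outcome before any interval exists. So the claim that prompt return leads to vaccination is inference, and the scenarios built on it may not apply. The shared-cause scenario could still apply to survey timing, but its common cause is assumed too.

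Finally, the covariate might be coded as a disruption period or a clinic indicator, a detail that an analysis plan could settle. That is possible. But the article names the time interval itself and ties it to adjustment of all measures, so the point concerns a stated choice and not a missing detail. A conditional analysis that can mislead when invoked is worth correcting, especially as the article states no criterion for invoking it.

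**Conclusion.** The concern holds in conditional form. Once triggered, the fallback may condition the arm comparison, including the primary vaccination outcome, on a post-randomisation variable that the intervention could affect. The result is then not the total effect, and can be biased, if the arm shifts follow-up time and that time affects vaccination or shares a cause with it. Without such a shift no spurious effect arises. For vaccination the adjustment brings no clear gain, because the record period already defines the outcome.

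The odds ratios and power losses rest on assumed shifts, slopes, correlations and vaccination rates, on independent participants, and on the raw interval being the covariate. They show direction and possible size, and are not estimates for this trial. A reader might take the fall from 80% to about 5% as a forecast; the documents do not support that. The point merits a wording change and does not call the design into question.

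**What to change.** In Phase 3: Data Management and Quantitative Analysis:

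- Limit covariates in the main adjusted arm comparison to factors fixed before the intervention, for example preintervention score, age and calendar period of enrolment.
- Keep the comparison without post-randomisation covariates as the main result, whether or not the fallback is invoked.
- Count vaccination within the same 6-month window from enrolment for every youth.
- Report time to follow-up by arm descriptively.
- Label any GEE adjusted for follow-up time as a sensitivity analysis, mainly for the survey measures.

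The cost is a few sentences. The article does not say whether the record extract includes vaccination dates; if it does not, the request to clinics needs that field. The small downside is that externally caused variation in survey timing is not modelled in the main result.
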